### **7.3 Withdrawal of individual subjects**

Subjects can leave the study at any time for any reason if they wish to do so without any consequences. The investigator can decide to withdraw a subject from the study for urgent medical reasons. Reasons for withdrawal will be documented.

### **7.4 Replacement of individual subjects after withdrawal**

When subjects withdraw from the study they will be replaced in order to obtain a sample size of 300 subjects. The maximum number of drop outs that will be replaced is 50.

### **7.5 Follow-up of subjects withdrawn from treatment**

If medically necessary, subjects will be monitored after withdrawal medically by the principal investigator.

### **7.6 Premature termination of the study**

The BCG vaccine is considered to be a safe vaccine, therefore, no serious adverse events are expected. However, if there is sufficient ground that continuation of the study will jeopardise subject health or safety, the study will not be continued before the cause of the SAE is known and a further positive decision by the accredited METC is given.

## **8. SAFETY REPORTING**

### **8.1 Temporary halt for reasons of subject safety**

In accordance to section 10, subsection 4, of the WMO, the sponsor will suspend the study if there is sufficient ground that continuation of the study will jeopardise subject health or safety. The sponsor will notify the accredited METC without undue delay of a temporary halt including the reason for such an action. The study will be suspended pending a further positive decision by the accredited METC. The investigator will take care that all subjects are kept informed.

### **8.2 AEs, SAEs and SUSARs**

#### **8.2.1 Adverse events (AEs)**

Adverse events are defined as any undesirable experience occurring to a subject during the study, whether or not considered related to the vaccination. All adverse events reported spontaneously by the subject or observed by the investigator or his staff will be recorded.

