**Main study parameters/endpoints:**

- 1) Ex vivo cytokine production by immune cells before and after vaccination upon stimulation with different pathogens will be measured by ELISA.
- 2) Immune cell subpopulations will be assessed by FACS.
- 3) Genetic variations that influence training will be assessed in DNA samples by Human Core SNP array from Illumina.
- 4) Epigenetic, transcription and metabolomic profiles before and after vaccination will be compared.
- 5) The correlation between the microbiome and the immune responses will be assessed.
- 6) The relationship between trained immunity and other host factors such as age, sex and metabolic state will be investigated.
- 7) The impact of environmental factors (e.g. season, stress) on induction of adaptive and innate immunity will be studied.

**Nature and extent of the burden and risks associated with participation, benefit and group relatedness:** Currently there is no known direct benefit to the study participants. The risks are negligible. Vaccination could cause pain, scarring at the site of injection, headache and fever. Venipuncture could result in minor discomfort and local hematoma formation could occur at the site of the blood drawing. Experienced personnel will be used in order to

minimize the minor side-effects. Volunteers have to spend 3 short visits and each visit they are asked to fill in a questionnaire and to donate a certain amount of blood.

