### **3.5 Questionnaires**

At all time points of blood collection, participants are asked to complete a questionnaire addressing questions on: current or previous infections (flu, fever, cold), substance abuse, perceived physical stress, medication (NSAIDs, aspirin), vaccination history (e.g. flu vaccine) etcetera.

Vaccinations will be performed at the outpatient clinic of the Department of Internal Medicine Radboudumc, and the experimental studies will all be performed at the laboratory of Experimental Internal Medicine at the Radboudumc.

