#### **6.4 Summary of known and potential risks and benefits**

Apart from protection against extrapulmonary infection with *Mycobacterium tuberculosis* and *Mycobacterium leprae*, there are no expected benefits for participants in the study.

Potential risks include only the side effects of the vaccine, of which localized skin reactions are most common. The local reaction after BCG vaccination is usually mild and self-limiting. Less common are fever and headache after vaccination and if they occur they are typically mild. Enlargement of the axillary lymph nodes may occasionally occur after vaccination but will usually regress spontaneously after a few months.

After vaccination, seroconversion to Mantoux testing has been described to occur in 41.8% of the individuals, which decreases to 21.2% after 10 years (Farhat, Greenaway, Pai, & Menzies, 2006). For these reasons Mantoux testing cannot be used as a diagnostic test for tuberculosis in the future. However, other diagnostic tools are available such as the Quantiferon test and chest X-ray.

Local haematoma formation could occur at the site of vena puncture. See also the summary of product characteristics for a list of side effects.

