### **Other procedures regarding subjects:**

#### **1) Questionnaires**

At all time points metadata will be collected using questionnaires. At the first visit this will be a more extensive list of questions regarding lifestyle, that will take about 20 minutes to complete. At all other time points the questionnaire will be shorter and will take about 5 minutes to complete. It addresses questions on current health status, level of physical stress etcetera (see the F1 questionnaire document for a complete overview).

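### Adverse events are collected only by spontaneous report or staff observation, and nothing visible links the visit questionnaire to the AE record, so fever, headache and axillary node enlargement may be under-recorded

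*Protocol*

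**What the plan says.** Section 8.2.1 gives a broad definition, "Adverse events are defined as any undesirable experience occurring to a subject during the study, whether or not considered related to the vaccination", followed by a collection rule: "All adverse events reported spontaneously by the subject or observed by the investigator or his staff will be recorded".

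The expected reactions appear in two places. The Summary says "Vaccination could cause pain, scarring at the site of injection, headache and fever". Section 6.4 lists the side effects of the vaccine, "of which localized skin reactions are most common", and continues: "Less common are fever and headache after vaccination and if they occur they are typically mild". On the regional reaction it says: "Enlargement of the axillary lymph nodes may occasionally occur after vaccination but will usually regress spontaneously after a few months".

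A questionnaire is completed at every blood draw. Section 3.5 summarises its topics, the first being "current or previous infections (flu, fever, cold"), and ends the list as open. Section 7.2 says of the follow-up visits: "At all other time points the questionnaire will be shorter and will take about 5 minutes to complete". It adds that the questionnaire covers present health among other things, and refers to a separate F1 document for the full content. Section 7.1.2 (item 5) classes the questionnaire data as metadata.

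The same section (item 6) schedules an examination of the vaccination site two weeks after vaccination, with a photograph and with scar size and local inflammation documented by an independent researcher.

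**The concern.** The collection rule is narrower than the definition it serves. A spontaneous report depends on the participant deciding that a symptom is worth mentioning, and staff can observe only what is present at a visit. A mild fever or headache that has resolved before day 14 is not there to be observed. The sponsor knows in advance what to ask about, sees every participant twice after vaccination, and has a questionnaire in hand each time, yet the stated AE rule does not use it.

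Two later commitments depend on the AE record. Section 8.4 follows all AEs until they have abated or stabilised, and an event that was never entered is not followed. Section 8.3 promises an annual report that includes a full safety analysis. At stake is whether those sections work from a complete list of non-serious, non-local reactions.

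**Working it through.** No arithmetic applies: the protocol attaches no rate, sample size or test to AE collection. The check is to take each expected reaction and ask what the visible text provides beyond spontaneous report or observation.

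| Expected reaction | Where named | Active collection described |
|---|---|---|
| Local skin reaction, scar | Summary; 6.4 | Yes: site examination and photograph at two weeks (7.1.2, item 6) |
| Pain | Summary | None described; the site record covers scar size and inflammation |
| Fever | Summary; 6.4 | Asked about, but as an example of infection (3.5) |
| Headache | Summary; 6.4 | None described |
| Axillary node enlargement | 6.4 | None described; no armpit examination among the procedures in 7.2 |

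**Does the questionnaire close the gap?** It could, but the text does not say so. Its stated purpose is metadata, and no section says that its answers are entered as AEs. An answer to a prompt is not spontaneous, and it is debatable whether staff have observed something by reading a form. Section 8.2.1 as worded therefore does not clearly cover it.

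**Why the placing of fever matters.** At day 0, grouping fever with flu and cold is natural, because section 4.3 excludes recent febrile illness. At day 14 the interval since the previous visit is the period just after vaccination, when a fever may be either an infection or the reaction named in 6.4. The visible text gives no way to separate the two, such as an onset date relative to vaccination.

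**Why node enlargement matters.** It is the one named reaction said to last for months. Month 3 is the last visit, so an enlarged node may still be present then. Section 8.4 would require it to be followed, but only if it has been recorded.

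**What cannot be checked.** F1 is not among the documents at hand. The topic list in 3.5 is open-ended, and 7.2 adds present health. Symptom items may exist there.

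**The case against.** The strongest reply is that the questionnaire's content is unknown. A bracket in a topic summary is not a coding rule, and F1 may already ask about each of these symptoms. This stands. A reader might infer that vaccine reactions are in fact missed or misfiled, or that node enlargement is never asked about. The documents do not support either statement.

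Second, staff observation can be read generously, to include what staff learn at visits or from a completed form. In addition, a fever reported as an infection still meets the broad AE definition, so its label does not remove it. This is a fair reading, but it is not written down, and one sentence would settle it.

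Third, the most common reaction is actively examined in everyone, and what remains is described as less common, mild or occasional. That is correct and narrows the point to the non-local reactions and pain. No section says that the site findings enter the AE record either, although the wording on staff observation could cover them.

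Fourth, unsolicited collection is a defensible choice for a long-used vaccine in a single-arm mechanistic study where, local skin findings apart, reactogenicity is not an objective. That limits the weight of the point, but it does not make the stated rule the better method when the questionnaire is already in use.

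**Conclusion.** The point holds as a cheap improvement to the safety data. The visible protocol fixes AE collection as spontaneous or observed, solicits no non-local reaction as a possible reaction, and does not link the questionnaire to the AE record. Fever, headache and node enlargement may be under-recorded, and a fever may be recorded only as infection. The conclusion assumes that F1 contains neither dedicated items nor an instruction to transfer answers. If it has the items, only the missing link remains.

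No size can be given. The protocol states no incidence for these reactions and no capture rate for spontaneous reporting, so any count of lost events would be invented.

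Two stronger readings should be resisted. A reader might infer that the negligible-risk classification depends on this trial's AE counts. Section 12.1 rests it on prior use of the vaccine, its known side effects and the product information, before anyone is enrolled. A reader might also infer that a response to the vaccine is analysed as if it were an exposure. Section 9.1 specifies no analysis with post-vaccination fever or infection as an explanatory factor, and infection is not among the environmental factors the protocol names. The primary analysis is unaffected.

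**What to change.** In section 8.2.1, state that AEs are also solicited at day 14 and month 3 through the existing questionnaire. The changes are:

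- Add a short fixed list: fever, headache, arm pain and swollen armpit glands. Each is answered yes or no, with start date and with duration or ongoing.
- Ask about fever separately from infection, with its onset date relative to vaccination.
- State that positive answers are entered in the AE record, so that the follow-up rule in 8.4 applies to them.

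Check F1 first. If it already contains these items, add only the sentence linking the answers to the AE record.

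The cost is a few lines on a questionnaire of about five minutes and a wording change in 8.2.1. The downside is more minor AEs to record and a less favourable reported AE rate.

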#### **8.2.2 Serious adverse events (SAEs)**

A serious adverse event is any untoward medical occurrence or effect that:

- results in death;
- is life threatening (at the time of the event);
- requires hospitalisation;
- results in persistent or significant disability or incapacity;
- is a congenital anomaly or birth defect; or
- any other important medical event that did not result in any of the outcomes listed above due to medical or surgical intervention but could have been based upon appropriate judgement by the investigator.

An elective hospital admission will not be considered as a serious adverse event.

As the BCG vaccine is considered to be safe, no SAEs are expected. However, in case of a SAE the condition of the volunteer will be evaluated by the independent MDs, who can decide to break the randomization code. If needed, the volunteer will be admitted to our hospital or will be evaluated by an independent MD at the outpatient clinic.

The investigator will report all SAEs to the sponsor without undue delay after obtaining knowledge of the events.

The sponsor will report the SAEs through the web portal *ToetsingOnline* to the accredited METC that approved the protocol, within 7 days of first knowledge for SAEs that result in death or are life threatening followed by a period of maximum of 8 days to complete the initial preliminary report. All other SAEs will be reported within a period of maximum 15 days after the sponsor has first knowledge of the serious adverse events.

### **8.2.3 Suspected unexpected serious adverse reactions (SUSARs)**

Adverse reactions are all untoward and unintended responses to an investigational product related to any dose administered.

Unexpected adverse reactions are SUSARs if the following three conditions are met:

1. the event must be serious (see chapter 9.2.2);
2. there must be a certain degree of probability that the event is a harmful and an undesirable reaction to the medicinal product under investigation, regardless of the administered dose;
3. the adverse reaction must be unexpected, that is to say, the nature and severity of the adverse reaction are not in agreement with the product information as recorded in:
  - Summary of Product Characteristics (SPC) for an authorised medicinal product;
  - Investigator's Brochure for an unauthorised medicinal product.

The sponsor will report expedited the following SUSARs through the web portal *ToetsingOnline* to the METC *<reporting via webportalToetsingOnline is only applicable for investigator initiated studies>*:

- SUSARs that have arisen in the clinical trial that was assessed by the METC;
- SUSARs that have arisen in other clinical trials of the same sponsor and with the same medicinal product, and that could have consequences for the safety of the subjects involved in the clinical trial that was assessed by the METC.

The remaining SUSARs are recorded in an overview list (line-listing) that will be submitted once every half year to the METC. This line-listing provides an overview of all SUSARs from the study medicine, accompanied by a brief report highlighting the main points of concern.

The expedited reporting of SUSARs through the web portal Eudravigilance or *ToetsingOnline* is sufficient as notification to the competent authority.

The sponsor will report expedited all SUSARs to the competent authorities in other Member States, according to the requirements of the Member States.

The expedited reporting will occur not later than 15 days after the sponsor has first knowledge of the adverse reactions. For fatal or life threatening cases the term will be maximal 7 days for a preliminary report with another 8 days for completion of the report.

### **8.3 Annual safety report**

In addition to the expedited reporting of SUSARs, the sponsor will submit, once a year throughout the clinical trial, a safety report to the accredited METC, competent authority, and competent authorities of the concerned Member States.

This safety report consists of:

- a list of all suspected (unexpected or expected) serious adverse reactions, along with an aggregated summary table of all reported serious adverse reactions, ordered by organ system, per study;
- a report concerning the safety of the subjects, consisting of a complete safety analysis and an evaluation of the balance between the efficacy and the harmfulness of the medicine under investigation.

### **8.4 Follow-up of adverse events**

All AEs will be followed until they have abated, or until a stable situation has been reached. Depending on the event, follow up may require additional tests or medical procedures as indicated, and/or referral to the general physician or a medical specialist. SAEs need to be reported till end of study within the Netherlands, as defined in the protocol

### **8.5 [Data Safety Monitoring Board (DSMB) / Safety Committee]**

As we classify this study as a 'laag-risico onderzoek', with a 'verwaarloosbaar risico', once a year an independent competent colleague will perform the monitoring according to the provided guidelines by the NFU.

## 9. STATISTICAL ANALYSIS

### 9.1 Primary study parameter(s)

The first step in the analysis of this study will be to examine the induction of adaptive immune memory and trained immunity in the cohort and to determine the variation between subjects. Inter-individual variation of the cytokine responses will be evaluated using Fligner-Killeen test of homogeneity of variances. The variance for each of the stimulation conditions will be compared to the unstimulated state.

Cytokine production upon *ex vivo* restimulation of monocytes before vaccination will be compared with cytokine levels after vaccination with BCG. Since every subject will be compared to themselves and cytokine production is considered to be non-parametric, the Wilcoxon signed rank test will be used in order to calculate the enhanced function of monocytes (trained immunity).

Results will be expressed as means  $\pm$  standard errors of the means (SEM). P values less than 0,05 are considered statistically significant.

All tests will be performed on GraphPad Prism 6.0 software (GraphPad).

To determine and link genetic polymorphisms to trained immunity, genotype data will be analyzed using haploview software. The Wilcoxon signed rank test will be used in metabolomics and epigenomics studies in order to compare data before and after vaccination. Data validation will be essential to ensure that findings are not false positives.

Microbiome reads will be first processed using KneadData. This includes quality-trimming (trimmomatic parameters: MAXINFO:90:0.5), read-filtering based on a minimum read length of 60bp and removal of potential human contamination by filtering reads that aligned to the human genome (reference genome hg19). Quality-controlled, paired-end reads will be aligned against a database of unique clade-specific marker genes using bowtie2 and taxonomic profiles and inferred with MetaPhlAn 2.2 (Segata et al., 2012). For the subsequent analysis we will consider species as well as genus composition of the samples. Functional microbiome profiling will be done using HUMAnN2 (Segata et al., 2013). Briefly, reads will be mapped against a customized database of functionally annotated pangenomes only considering organisms that were identified during the taxonomic profiling step. Functional annotation of the protein-sequences in the pangenomes to their respective UniRef50 family will be provided.

Given the complexity and the amount of data that will be generated in this study, the statistical analyses will be performed in strong collaboration with bioinformaticians and systems biology experts from the group of Prof. [name] (Department of Genetics,

UMCG) and of Prof. [name] (Broad Institute at MIT/Harvard).

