### Specific research questions:

1. What is the variation of adaptive and trained immunity memory in a cohort of healthy volunteers after vaccination with BCG?
2. Which genetic polymorphisms modulate adaptive and trained immunity induced by BCG vaccination?
3. In which way does trained immunity alter the epigenome, transcriptome and metabolome of the host monocytes and do these changes correlate with trained immunity?
4. Is there a correlation between differences in the composition of the microbiome and the induction of adaptive memory and trained immunity?
5. Is the induction of trained immunity influenced by non-genetic host factors such as sex, age, substance abuse and metabolic state?

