### 4.4 Sample size calculation

The sample size calculation is not possible due to the variable frequencies of various traits in this study, such as SNP frequency and the variable prevalence of the microorganism classes in the microbiome. The size calculation will be variable depending on which type of polymorphism will be analyzed. The frequencies are not known and therefore power calculations are not possible to perform. Because our aim is to find new DNA polymorphisms that modulate training we need a larger sample size than the *in vivo* BCG studies that have been performed to date. To be able to detect any potential relevant SNPs, we decided to include 300 individuals, based on previous studies within the Human Functional Genomics Project.

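### Section 9.1 fixes results as mean ± SEM, which fits neither its rank test nor its question about variation between people

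*Protocol*

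**What the plan says.** Three statements in the protocol bear on this point.

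- **The question.** Research question 1 in section 2 reads: "What is the variation of adaptive and trained immunity memory in a cohort of healthy volunteers after vaccination with BCG". Section 9.1 takes this up at the start, where the analysis is "to determine the variation between subjects". It assigns a method: "Inter-individual variation of the cytokine responses will be evaluated using Fligner-Killeen test of homogeneity of variances". Each stimulation condition is compared with the unstimulated state.
- **The test of the vaccine effect.** For cytokines before against after vaccination, section 9.1 reasons that each subject serves as their own control and that "cytokine production is considered to be non-parametric, the Wilcoxon signed rank test will be used".
- **The reporting format.** The next paragraph of section 9.1 states "Results will be expressed as means" with the SEM as the error term, and names no exception.

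Section 4.4 sets the cohort at 300. The protocol names no median, interquartile range, SD, log scale, confidence interval or display of individual values.

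**The concern.** The reporting sentence conflicts with its surroundings in two ways.

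First, the plan sets aside a mean-based test because of how the data are distributed, then makes the mean its only stated estimate. If a few high producers dominate, the reported mean can move while the signed ranks barely change. The estimate and the p-value could then tell different stories.

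Second, the study is about differences between people in their response to BCG, yet the only dispersion figure prescribed for the results shrinks as n grows and does not describe those differences. A reader who wants the answer to research question 1 would find neither the spread nor the shape of the distribution in the prescribed format.

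The protocol states this format, so an analysis plan would have to depart from the sentence to report otherwise. It is not a detail left for later.

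**Working it through.** The protocol gives no SD, effect size or summary figure to reproduce. The inputs are n = 300 (section 4.4), the mean ± SEM format and the rank test (both section 9.1). The degree of skew is not in the document and is assumed.

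**1. SEM against spread.** SEM = SD/√n, so SD/SEM = √n for any distribution.

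- n = 300: √300 = 17.3
- n = 250 (illustrative): √250 = 15.8
- n = 150 (one sex, if the cohort splits equally): √150 = 12.2

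For normal data at n = 300, mean ± SEM spans 2Φ(1/17.32) − 1 = 4.6% of participants, against 68.3% for mean ± SD. This follows from n and says nothing about skew; lognormal data with log-SD 0.6 to 1.0 give 4.8% to 5.3%.

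**2. Mean against median under assumed skew.** For lognormal data with log-SD s, mean/median = exp(s²/2), and the share of people below the mean is Φ(s/2).

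| s (assumed) | mean/median | share below the mean |
|---|---|---|
| 0.6 | exp(0.18) = 1.20 | Φ(0.30) = 62% |
| 0.8 | exp(0.32) = 1.38 | Φ(0.40) = 65% |
| 1.0 | exp(0.50) = 1.65 | Φ(0.50) = 69% |

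A wider range of s, 0.5 to 1.5, puts the ratio at 1.13 to 3.08 and the mean at the 60th to 77th percentile.

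**3. What median and interquartile range would show instead.** With median 1, the interquartile width is exp(0.6745s) − exp(−0.6745s), and the SEM is exp(s²/2)·√(exp(s²) − 1)/√300. The interquartile width divided by the full mean ± SEM width (2 × SEM) is:

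- s = 0.5: (1.401 − 0.714)/(2 × 0.035) = 9.9 (using the unrounded SEM)
- s = 1.0: (1.963 − 0.509)/(2 × 0.125) = 5.8
- s = 1.5: (2.750 − 0.364)/(2 × 0.518) = 2.3

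The visible change in the bars therefore depends on the unknown skew. It is not a fixed 17-fold.

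**4. The scale of the signed rank test.** The test is not invariant to taking logs of paired values. Take three invented pairs: 1000→600, 10→40 and 10→60.

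- Raw differences: −400, +30, +50. The absolute values rank 3, 1, 2, so W+ = 3 and W− = 3.
- Log ratios: −0.51, +1.39, +1.79. The absolute values rank 1, 2, 3, so W+ = 5 and W− = 1.

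Section 9.1 names no log scale, so as written the test ranks raw differences. An effect estimate on log ratios matches the test only if the test is run on log ratios too.

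**The case against.** The strongest reply is that the SEM is a legitimate, clearly labelled measure of the precision of a mean. The ratio of 17.3 is an identity that holds in any study of 300 people, and a reader can recover the SD by multiplying back. That stands. One might infer that the plan understates variation 17-fold. The document does not support this, because the bars mislead only if they are taken for spread.

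The plan also does not ignore research question 1, since it gives inter-individual variation its own test. That stands too, but Fligner-Killeen yields a test of equal variances between conditions, not a description of how widely people differ.

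The SEM sentence follows the before/after comparison and may have been meant for that alone. On that reading the mean still sits beside a rank test, and no spread measure is prescribed for research question 1.

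One might also infer that the SEMs are per visit and ignore the pairing, or that readers are left without any interval for the vaccine effect. The protocol does not say whether the SEM belongs to each visit or to the within-person change. If it belongs to the change, it respects the pairing and gives an approximate interval.

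Finally, right skew is an inference from the word non-parametric. If within-person differences were symmetric, their mean and the signed rank location would coincide.

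**Conclusion.** The point holds as a reporting defect of minor to moderate weight. The prescribed mean ± SEM fits neither the rank test nor the question about variation between people.

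That the SEM does not describe spread needs no assumption about the data; at the planned 300 it is SD/17.3. That the mean is a poor centre is conditional on skew: 1.20 to 1.65 times the median for an assumed log-SD of 0.6 to 1.0. That the estimate and the p-value might diverge is a possibility that depends on asymmetric within-person changes, and nothing in the document shows that it will happen.

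It would be wrong to conclude that the inference is damaged. The Wilcoxon and Fligner-Killeen tests, their p-values, the data collected and the sample size are the same whichever summary is reported.

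**What to change.** Replace the mean ± SEM sentence in section 9.1 with the following:

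- For each stimulus, cytokine and visit, report the median and interquartile range, or the geometric mean with the SD on the log scale.
- For each post-vaccination visit, report the within-person change with a 95% confidence interval from the Hodges-Lehmann estimator, on the same scale as the signed rank test. As now written, that means raw differences. If a fold change is wanted, run the test on log ratios as well and back-transform the estimate and interval.
- Plot individual paired values.
- Keep the SEM only where the precision of a mean is what is meant, and say whether it refers to a visit or to the change.

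The summaries and plots cost a few lines of text, with no extra data, assays or participants. Keeping raw differences leaves the planned p-values as they are. Moving to log ratios would change them, so that choice should be written down before the data are analysed.
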